## Abstract

**Background:**

Although results from in vitro studies and small randomized controlled trials have shown positive effects of Dazhu hongjingtian injection (DZHJTI) on acute ischemic stroke (AIS), their generalizability to routine clinical practice remains to be established.

**Objective:**

The primary aim of this study is to evaluate the effectiveness of DZHJTI treatment for AIS with regard to changes in the stroke-related neurological deficit from baseline to outpatient follow-up, mortality, subsequent vascular events, disability, and traditional Chinese medicine syndrome in real-world clinical settings. By monitoring for adverse events or significant changes in vital signs and laboratory parameters, we also aim to assess the safety of DZHJTI.

**Methods:**

This prospective, multicenter cohort study plans to enroll 2000 patients with AIS within 14 days of symptom onset from 30 hospitals across China. Eligible patients will be followed up for 6 months after initiating medication treatments. The primary outcome will be the change in the National Institute of Health Stroke Scale score from baseline to outpatient follow-up. The secondary outcomes include overall mortality, stroke recurrence, new-onset major vascular events, global disability, and improvement of traditional Chinese medicine syndrome in 6 months. Adverse events or clinically significant changes in vital signs and laboratory parameters, regardless of the severity, will be recorded during the trial to assess the safety of DZHJTI. An augmented inverse propensity weighted estimator will be used to reduce variability and improve accuracy in average treatment effects estimation.

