### Data Collection and Monitoring

Trained research personnel at each participating site will collect baseline data during patient admission, including prehospital care and treatment, prestroke symptoms, and the NIHSS. They will also conduct assessments using the prestroke modified Rankin Scale scores and Barthel Index. Patient information, including demographics, medical and family history, physical examination, auxiliary examination, risk factor assessment, and clinical diagnosis, will be obtained from medical records. The classification of stroke etiology, related complications, and new cerebrovascular events will be documented, and the etiology of AIS will be determined according to the Trial of Org 10172 in Acute Stroke Treatment criteria [17]. Besides standard therapies, the administration of DJHJTI during hospitalization will be documented by the research team.

The collection and reporting of data will use a secure electronic data capture (EDC) system that follows the current clinical protocol and provides each patient with a unique ID. Authorized research personnel can access the EDC system both on personal computers and smartphones, enabling them to complete data collection during daily ward rounds. An overview of the measurement data collection schedule is shown in Table 1. In the EDC system, personal identifiers such as names, ID numbers, and contact information are removed or replaced with unique codes to ensure participant anonymity.

**Table 1 table1:** Schedule of assessments in the cohort study.

Participant assessment	Time point and form				
	Baseline (acute phase)		Follow-up 1	Follow-up 2	Follow-up 3
	Admission	Discharge	1 month	3 months	6 months
	Visit	Visit	Visit or telephone interview	Visit or telephone interview	Visit or telephone interview
Eligibility screen	✓^a^				
Informed consent	✓				
Demographic and anthropometric data	✓				
TCM^b^ questionnaire	✓				
NIHSS^c^	✓	✓			
mRS^d^	✓	✓	✓	✓	✓
BI^e^			✓	✓	✓
Laboratory examination	✓	✓	+^f^	+	+
Imaging examination	✓	✓	+	+	+
Admission status		✓			
Discharge status		✓			
Follow-up interview			✓	✓	✓
AE^g^		+	+	+	+
Outcomes		+	+	+	+

^a^Required data.

^b^TCM: traditional Chinese medicine.

^c^NIHSS: National Institutes of Health Stroke Scale.

^d^mRS: modified Rankin Scale.

^e^BI: Barthel Index.

^f^Optional data to be collected based on the actual occurrence of related events in patients.

^g^AE: adverse events.

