### Follow-Up Procedures

All patients will be identified and followed up using individual identity cards, which are mandatory for all Chinese citizens, enabling unambiguous linkages. Research personnel will conduct regular face-to-face or telephone follow-up at 1, 3, and 6 months after stroke onset. Information on patient outcomes, including mortality, functional status, activities of daily living, cognitive function, and cardiovascular or cerebrovascular events, will be obtained during follow-up. Mortality will be confirmed through a death certificate issued by the local civil registry or the attending hospital. New cardiovascular or cerebrovascular events requiring rehospitalization will be verified by the discharge diagnosis. In the absence of hospitalization, a committee responsible for determining end points will evaluate suspected recurrent cardiovascular or cerebrovascular events [18].

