### Outcomes

In this study, the primary outcome will be the distribution of scores on the NIHSS before and after treatment among patients. Secondary outcomes will be assessed at different follow-up visits and will include death, a composite of new clinical vascular events, neurological function, and improvement of traditional Chinese medicine syndrome. Safety assessment will be performed by monitoring adverse events. The complete study outcomes are illustrated in Table 2.

**Table 2 table2:** Outcome variables and definitions.

Outcome variables		Definitions

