**Primary outcome**		
	Improvement degree of clinical NIHSS^a^ scores	Basic recovery (NIHSS score decreased by more than 90%) Significant improvement (NIHSS score decreased by 46%-89%) Improvement (NIHSS score decreased by 18%-45%) No change (NIHSS score decreased 0%-18% or increased<18%) Deterioration (NIHSS score increased more than 18%) The basic recovery, significant improvement, and improvement were regarded as effective. The no change, deterioration, and death were regarded as inefficient [19]

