### Sample Size

According to the previous studies, the ineffective rate assessed by NIHSS score (percentage of patients experiencing no change and deterioration) in controls was 8.75% (7/80), and the ratio of cases to controls was 0.31 [14]. To test the hypothesis that adjuvant treatment with DZHJTI significantly reduces the ineffective rate with a 2-sided α of .05, power of 0.80, and a 20% (n=248) dropout rate, a sample size of 619 cases in each group is required. Nevertheless, a sufficiently large sample size is also necessary to reduce the bias in real-world studies. Therefore, a total of 1000 case participants per group will be included.

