However, it is important to note that biases are common in real-world studies. Participants from different study sites may differ in characteristics, and combined treatments can vary widely. Additionally, incomplete data can be a significant issue with real-world data sources. Therefore, we plan to use the AIPW estimator, which involves a doubly robust procedure to minimize bias if either the treatment or outcome model is correctly specified [27]. The accuracy of the AIPW estimator for the average treatment effect has been demonstrated under different scenarios of misspecification [27]. To perform propensity score analysis when data are missing, we will conduct the analysis in each imputed data set and then combine the estimates of the treatment effect to obtain an overall estimate. This method has been demonstrated to be unbiased under a missing at random mechanism, and Rubin rules have been shown to provide reliable variance estimates and show good balancing properties [20].

Another key consideration in this trial is selecting an appropriate primary outcome, which depends largely on the disease and should reflect the treatment effect and expected mechanism. NIHSS is a tool used to objectively quantify neurological impairment after stroke [28], while the modified Rankin Scale and modified Barthel Index are commonly used scales to measure disability or dependence in daily activities in patients with stroke or other neurological dysfunction [29]. Previous studies on herbal injection often have limited follow-up periods of up to 3 months due to drug metabolism. However, since AIS neurological function recovery is a slow process, with the main recovery period occurring within 2 to 6 months after onset [30], we evaluated the effects of DZHJTI on neurological recovery for a period of 6 months after discharge from the hospital.

To our knowledge, this is the first and largest prospective cohort study in China that evaluates the real-world effectiveness and safety of DZHJTI in the treatment of AIS. It may provide additional clinical evidence, including the duration of response, long-term drug effectiveness, and subgroup efficacy data of DZHJTI treatment for patients with AIS under the influence of other confounding factors. Ultimately, the results of this study will help optimize individualized interventions with DZHJTI for the treatment of AIS in China, leading to better patient outcomes and more standardized treatment practices.

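### The primary NIHSS outcome is set at outpatient follow-up, but NIHSS is scheduled only at admission and discharge, and the primary variable is worded inconsistently

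*Protocol article*

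**What the plan says.** **Time point.** The Abstract's Objective describes "changes in the stroke-related neurological deficit from baseline to outpatient follow-up", and its Methods paragraph repeats this for the primary outcome: "The primary outcome will be the change in the National Institute of Health Stroke Scale score from baseline to outpatient follow-up". Table 1 (Data Collection and Monitoring) ticks NIHSS at admission and at discharge, and places both columns under the baseline, acute-phase heading. The NIHSS cells at 1, 3 and 6 months are empty, and the form of those contacts is "Visit or telephone interview". Follow-Up Procedures agrees on the form: "Research personnel will conduct regular face-to-face or telephone follow-up at 1, 3, and 6 months after stroke onset". Its list of information gathered at follow-up covers mortality, function, daily living, cognition and vascular events, but not NIHSS.

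**Variable.** The Outcomes section states that "the primary outcome will be the distribution of scores on the NIHSS before and after treatment among patients" and refers the reader to Table 2. Table 2 defines five classes of percentage change in NIHSS and collapses them to two: "The no change, deterioration, and death were regarded as inefficient", with the three better classes counted as effective. The Sample Size section plans on "the ineffective rate assessed by NIHSS score (percentage of patients experiencing no change and deterioration", which was 8.75% (7/80) in controls.

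**The concern.** A primary outcome needs one variable, measured at one stated time, with a scheduled assessment at that time. Here the stated time and the schedule disagree. A site that follows Table 1 will record no NIHSS after discharge, so the outcome announced in the Abstract would have no follow-up values for any patient.

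What would be collected answers a different question: change during the hospital stay, read at a time that differs from patient to patient. In a non-randomised comparison the length of stay may also differ between groups.

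The varying description of the variable adds to this. A mean change, a shift across ordered classes and a difference in the proportion ineffective are different effects. They treat death differently, and only one of them was used to size the study.

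**Working it through.** The point rests on no sample-size figure. The passages are set side by side, followed by a short check of the class boundaries.

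**1. What each place specifies**

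| Place | Variable | Post-treatment time | Death |
|---|---|---|---|
| Abstract, Objective | Change in neurological deficit | Outpatient follow-up | Listed separately |
| Abstract, Methods | Change in NIHSS score | Outpatient follow-up | Separate secondary outcome |
| Outcomes text | Distribution of NIHSS scores | After treatment, not fixed | Separate secondary outcome |
| Table 2 | Five classes, collapsed to effective/inefficient | None given | Counted as inefficient |
| Sample Size | Ineffective rate, 7/80 = 0.0875 | None given | Not named |

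**2. What the schedule collects (Table 1, five time points)**

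- NIHSS: 2 of 5 (admission, discharge); 0 of the 3 follow-up contacts.
- mRS: 5 of 5.
- Barthel Index: 3 of the 3 follow-up contacts.

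Discharge cannot easily be read as outpatient follow-up, because Table 1 groups it with the acute phase and numbers the follow-ups from 1 month.

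**3. Which definitions can be computed from the scheduled data**

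- Abstract wording: no. It needs an outpatient NIHSS, and none is scheduled.
- Outcomes text, Table 2 and Sample Size: yes, if the later score is the discharge score. None of the three says so.

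**4. Which definition the planning supports**

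The Sample Size section gives a control proportion and no standard deviation or mean difference. It therefore supports the binary outcome, and power for the change score cannot be worked out from the article.

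**5. Class boundaries in Table 2**

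Percentage decrease = 100 × (baseline − later) / baseline. Baselines run from 6, because scores of 0 to 5 are excluded, to 42, taken here as the top of the scale. Scores are whole numbers and percentages are left unrounded.

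- 10 to 1: 100 × 9/10 = 90.0%. This is neither above 90% nor within 46% to 89%. Decreases above 89% and up to 90% can occur at baselines 10, 19, 20, 28, 29, 30, 37, 38, 39 and 40.
- 11 to 6: 100 × 5/11 = 45.45%. This falls between the classes ending at 45% and starting at 46%. Such values can occur at baselines 11, 22, 24, 31, 33, 35, 37 and 42.
- The classes on both sides of each gap are effective, so neither gap changes the binary outcome.
- The shared endpoint at 18% would cross the effective/inefficient line. However, exactly 18% is 9/50 and needs a baseline divisible by 50, so it cannot occur between 6 and 42. It matters only if percentages are rounded first: 2/11 = 18.18% would become 18%.

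**The case against.** **Table 1 may be the faulty side.** It has other gaps. The text has the Barthel Index assessed at baseline but the table does not tick it there. The TCM questionnaire is ticked only at admission, although improvement in TCM syndrome at 6 months is a secondary outcome. This stands: one cannot say that no outpatient NIHSS will ever be recorded, only that the passages conflict and none is scheduled.

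**The body of the article largely points to one variable.** The Outcomes section sends the reader to Table 2, and the sample size uses nearly the same binary rate. The Abstract and the opening sentence on outcomes may simply be loose summaries. This largely stands, and it is why the binary outcome is the natural one to keep. It does not supply a time point or settle how death is counted.

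**The analysis plan predates the study.** The article says a statistical analysis plan was developed before the cohort began. A reader might infer that the primary test could be chosen after seeing the data. The documents do not support that, since the unseen plan may fix the test. Any inflated false-positive rate would need an assumed NIHSS distribution and a rule of claiming whichever test succeeds, and the article states no such rule.

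**The Discussion does not promise NIHSS at 6 months.** It says "we evaluated the effects of DZHJTI on neurological recovery for a period of 6 months after discharge from the hospital", in a paragraph that covers NIHSS, mRS and the Barthel Index together. That sentence does not name NIHSS, and the other two scales are scheduled to 6 months. This stands, so the sentence is not counted as part of the contradiction.

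**Conclusion.** The conflict is real and should be resolved before analysis. Two statements in the Abstract place the primary outcome at outpatient follow-up; the schedule has NIHSS at 0 of 3 follow-up contacts, and the text on follow-up does not add it. The primary variable is worded in several ways, death is handled differently in Table 2 and Sample Size, and the Outcomes text and Table 2 fix no post-treatment time.

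A reader might conclude that no primary analysis can be run at all. That goes too far: it holds for the Abstract's wording only. For the other definitions the defect is ambiguity.

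A reader might also put a size on the bias from comparing groups at discharge. The article gives neither length of stay nor rate of recovery, so no figure can be supported. Whether the 7/80 included deaths depends on a cited source that is not at hand.

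The class gaps are minor. This part assumes whole-number scores, baselines of 6 to 42 and unrounded percentages.

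**What to change.** State one primary variable and one time point in the same words in the Abstract (Objective and Methods), the Outcomes text, Table 2 and Sample Size. The ineffective rate, counting no change, deterioration and death, is preferable because Table 2 defines it and the sample size is built on an almost identical rate. Name death in Sample Size, or say that the planning rate omits it. Make the change score and the class distribution secondary.

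Then choose one of two time points:

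- **(a) Admission to discharge.** Drop outpatient follow-up from the Abstract, and say plainly that this is an in-hospital outcome at a variable time. Report time from admission to discharge by group, or adjust for it; adjustment is better kept as a sensitivity analysis, since length of stay is determined after treatment starts. Rest longer-term claims on mRS and the Barthel Index, already scheduled to 6 months.
- **(b) Outpatient follow-up.** Tick NIHSS in Table 1 at one named in-person visit and state its time origin, since the article counts 6 months variously from start of medication, stroke onset and discharge. Say how scores missing through telephone contact are handled; the article describes multiple imputation for covariates only.

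Write Table 2's classes as contiguous half-open intervals on the unrounded percentage, so that each patient falls in exactly one.

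Cost: option (a) is mainly wording but narrows the stated objective. Option (b) adds an assessment and accepts missing values, including for patients already past that visit. Recruitment began in November 2022, so either change should be a dated amendment made before outcomes are compared between groups.

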**Results:**

The clinical trial registration was approved in October 2022, and the recruitment and enrollment of participants started in November 2022. The study’s outcomes are expected to be published in 2025 in reputable, peer-reviewed health-related research journals.

**Conclusions:**

This real-world cohort study is the first to assess the effectiveness and safety of DZHJTI in treating AIS. It may provide additional clinical evidence, including the duration of response, long-term drug effectiveness, and subgroup efficacy data. The study results will be valuable for clinicians and patients seeking optimal treatment for AIS and could lead to better use of DZHJTI and improved patient outcomes.

**Trial Registration:**

ITMCTR ITMCTR2022000005; http://tinyurl.com/554ns8m5

**International Registered Report Identifier (IRRID):**

DERR1-10.2196/52447

## Introduction

The high morbidity, mortality, and disability rates associated with stroke impose a significant health and economic burden not only in China but globally [1]. The annual stroke mortality rate in China is approximately 153.9 per 100,000 people, which is 4 times that of American and European countries [1-3]. As the most common subtype of stroke, ischemic strokes accounted for 82.6% (2,818,875/3,411,168) of stroke cases in China admitted in 2019 [4]. Despite receiving guideline-recommended care, including intravenous thrombolysis and endovascular therapy, many patients with stroke continue to experience nerve dysfunction. Recent research conducted in 30 provinces of China revealed that up to 78.7% of first-ever stroke survivors developed poststroke cognitive impairment within 3-6 months following the initial stroke event [5]. This highlights the urgent need to identify a medication with proven efficiency and safety in improving neurofunctional recovery, thereby alleviating the substantial burden on patients and the health care system.

Dazhu hongjingtian (DZHJT) or *Rhodiola wallichiana* var *cholaensis* (Praeger) SH Fu belongs to the family Crassulaceae in the genus *Rhodiola*. Plants of this genus have a long history of traditional use and are included in the official pharmacopeia of Asia, Europe, North America, Latin America, Oceania, and Africa, which is attributed to their proven efficacy in stimulating the nervous system, alleviating fatigue, and preventing high altitude sickness [6,7] (Figure 1). Rhodiola dietary supplements have been recognized by the European Food Safety Authority for their contribution to optimal mental and cognitive activity [8]. DZHJT injection (DZHJTI) is produced from dried roots and stems of DZHJT using processes approved by the Food and Drug Administration of China. Extensive research on the chemical constituents of DZHJTI has identified a total of 49 compounds using ultra-high–performance liquid chromatography coupled with quadrupole time-of-flight mass spectrometry analysis, and a fingerprint has been established by high performance liquid chromatography [9,10]. The primary active constituent of DZHJT, salidroside, has demonstrated various biological activities in both in vitro and in vivo studies, including effects on the central nervous system, cardiac vessel dilation, antihypoxia, and anti-inflammatory properties, among others [11-13].

**Figure 1 figure1:**
[figure not shown]
Worldwide patent application for Rhodiola. Data collected from the Lens (searching term: Rhodiola) as of July 20, 2023.

Several clinical studies have investigated the effects of DZHJTI on acute ischemic stroke (AIS). A pooled analysis of 18 trials involving 1713 participants demonstrated that DZHJTI combined with guideline-recommended therapy was superior to the control group in decreasing the National Institute of Health Stroke Scale (NIHSS; standardized mean difference –0.77, 95% CI –1.52 to –0.02). Moreover, when combined with basic therapy, DZHJTI can also significantly improve the whole blood viscosity, plasma viscosity, and level of fibrinogen, as well as decrease fasting blood glucose and levels of total cholesterol [14]. However, the relatively insufficient sample sizes and ambiguous study designs of previous studies urge high-quality real-world evidence from a rigorous research process.

To enhance the quality of clinical evidence and promote standardized development in clinical research related to traditional medicine on a global scale, we have established the International Traditional Medicine Clinical Trial Registry (ITMCTR), the world’s first international clinical trial registration platform for traditional medicine. This accomplishment has earned ITMCTR the distinction of being approved as a level 1 World Health Organization international clinical trial registration institution. ITMCTR became a member of the Primary Registry Network of the International Clinical Trials Registry Platform and the trials registered with ITMCTR have been added to the International Clinical Trials Registry Platform database. Building upon the foundation of this endeavor, we conducted a multicenter, prospective cohort study to assess the effectiveness and safety of DZHJTI as adjuvant therapy for patients with AIS in a real-world setting. With a complete and accurate study design and prospective registration, this study will provide qualified evidence for DZHJTI.

